# SCIENTIFIC / MEDICAL SECTION

## Scientific background

Personalized medicine is an important development in the individual treatment of patients and is based on individual and tailored medical decisions, practices and interventions. The terms personalized medicine, precision medicine and stratified medicine can be used interchangeably in this context.

Regional anaesthesia plays an important role in the context of perioperative medicine, thus providing the highest level of pain therapy during and after surgery. The use of ultrasound for the detection of peripheral nerves, the adjacent anatomy, the cannula and the spread of local anaesthetic solutions increased the efficacy of peripheral regional block techniques significantly and contributed to the reliability of these techniques. Despite a large body of evidence regarding ultrasound guided regional anaesthesia and improved regional block characteristics,^17^ there is limited knowledge in the field of personalized medicine in this context available.

A recent study illustrates gender differences in the CSA of cervical nerves with precise methods of measurements.^18^ A clinical study by Tang et al. shows prolonged blockade of the sciatic nerve in women with pre-existing diabetes.^11^ Unfortunately the authors did not measure the CSAs of individual nerves at the puncture site, but we speculate that the CSAs of nerves could correlate with the duration of sensory and motor blocks. Gender-dependent differences in the electrical conduction system of peripheral nerves could also influence the PD characteristics of regional blocks. Fujumaki et al. shows in this context a greater sensory nerve action potential of upper limb nerves in healthy females as compared with healthy men.^19^ Interestingly, these differences were only shown in upper, but not in lower limb nerves.

Conversely, Cullion et al. did not find differences of PD characteristics of nerve blocks with bupivacaine in rats. They showed a duration of sensory blockade of 158.5 [139-190] minutes (median [interquartile range]) (males) compared to 173 [134-171] minutes (females) (p = 0.702) and a duration of motor blockade of 157 [141-171] minutes (males) compared to 172 [146-320] minutes (females) (p = 0.2786). A study by Gaudreault et al. investigated the relationship between PK parameters and nerve block characteristics, and did also not find biological gender related differences.

As described above, the limited number of studies in the field of regional anaesthesia and biological gender shows controversial results. Until today, no study investigates gender-specific PD and PK characteristics of peripheral nerve blocks. We therefore designed this prospective, single-centre study in volunteers to investigate the influence of biological gender (male and women) on ultrasound guided peripheral nerve blockade.

## Study groups and nerve block technique

In the present study, 90 healthy male and female volunteers will receive ultrasound guided ulnar nerve blockade. Ultrasound guidance is the golden standard in regional anaesthetic nerve blocks with high success rates and low complications in experienced hands.

Ulnar nerve blockade: The ulnar nerve can be visualized below the level of the sulcus of the ulnar nerve and proximal where the ulnar artery joins the nerve, between the *flexor carpi ulnaris, humeroulnar head of the superficial flexor digitorum and profound flexor digitorum muscles*. The ulnar nerve shows a constant sensory distribution pattern with the lowest intra- and interindividual variability compared with other sensory- and motor nerves supplying the hand.^20^ The following combination of drugs will be administered:

*Study group M:* Ropivacaine 0.75% (Volume 3.0mL = 22.5mg) will be administered perineural to the ulnar nerve

*Study group F:* Ropivacaine 0.75% (Volume 3.0mL = 22.5mg) will be administered perineural to the ulnar nerve

### Sequence of Nerve Blockades

On the study day, blockade of the ulnar nerve with the above-described drug will be performed.

### Dosing rationale

Three ml local anaesthetic is a larger volume as described in the literature to provide an ED95 for peripheral single nerve blockade.^21^ Therefore, a reliable complete blockade can be assumed with the dose which is used in this study. We decided to administer a pre-defined volume of LA to obtain comparable PK data.

## Assessment of sensory and motor blockade

*Sensory blockade* will be assessed via Pinprick testing (100 = no difference to the contralateral side, 0 = no sensory reception) at the hypothenar area in comparison with the contralateral side. Five areas of sensory supply are defined:

- dorsal side hypothenar muscles
- ulnar side hypothenar area
- palmar side hypothenar muscles
- fifth finger
- ulnar side fourth finger.

Short bevel needles are used for Pinprick testing. The tip of the needle will be applied with a force adequate to indent the skin without puncturing it, and this will produce a consistent painful sensation when applied to non-blocked areas. This kind of sensory testing is well described in the literature.^2,13^ Evaluation of skin temperature (which is also a factor of skin-sensitivity) will not be performed because of conflicting results in the literature and various factors influencing the measurements.^22^ In addition, the sympathetic portion of the ulnar nerve is unpredictable (different to e.g. the sciatic nerve, where a large portion of sympathetic fibres can be assumed).^23^

*Motor blockade* will be assessed via adduction of the thumb:

- 3 = no difference, adduction against contra-force possible
- 2 = slight difference, adduction against slight contra-force hardly possible
- 1 = significant difference, adduction without contra-force hardly possible
- 0 = no active adduction possible, paralysis

Sensory and motor testing will be performed at the following time points (min):

Baseline, 2, 4, 6, 8, 10, 15, 20, 30, 60 min after the block, and then every 30 min until Pinprick testing = 80 and motor-scale = 1.

*Onset of sensory and motor block* is defined as Pinprick = 0 in the hypothenar area (4 from 5 above-described areas to consider anatomical variations) and motor scale = 0.

Duration of sensory and motor block is defined as Pinprick testing = 80 in the hypothenar area and motor scale = 1.

We decided to define sensory block duration when Pinprick testing = 80 (and not back to 100) to avoid an extreme long duration of investigation. According to previous results with ropivacaine 0.75% (7.5 mg/ml), the duration of complete recovery from sensory block can be estimated with > 6 hours.

### Needle Material

22G 50mm Facette tip needles with an injection line (Polymedic™, te me na, Carrières sur Seine, France) will be used for nerve blockade.

### Sterility

The puncture area will be prepared in a surgical sterile manner. The ultrasound probe will be covered with a sterile ultrasound probe cover (SaferSonic Inc., Ybbs, Austria). Sterile ultrasound gel will be used as contact medium between the ultrasound probe and the skin (SaferGel, Ybbs, Austria).

## Nerve Measurements and Evaluation of Nerve Visibility^1^

Prior nerve blockade, the ulnar nerve will be scanned in the position as described above. For all scans, a high-end ultrasound device with a 15-6 MHz linear ultrasound probe will be used (SonoSite X-Port, SonoSite Inc., Bothell, WA, USA). The nerve will be traced until optimal visibility is obtained and the brightness will be standardized using the “Autogain” setting of the ultrasound machine. Since the ultrasound visibility of a nerve is a factor of differences in brightness between the tissues, the overall gain does not influence this proportion. Thereafter the nerve circumference will be measured with the internal area measurement tool.

Figures will be stored as JPEG files with the ulnar nerve in the centre of the screen. Ultrasound pictures will be analysed electronically by means of Photoshop 23.4.2 (Adobe Systems Inc., San Jose, CA, USA). The processed data files of one investigation series will be illustrated in the very same scale on personal computer display.

By using the moving tool from the Photoshop 23.4.2 software, the selected area will be moved to muscle and connective tissue around the nerve to the following positions: 3, 6, 9 and 12 o´clock. The above-described software-based measurements will be performed also for these selections.

Therefore 5 measurements (1 measurement for the nerve and 4 measurements for the surrounding tissue at 3, 6, 9 and 12 o´clock positions) will be performed in each volunteer and the grey scale difference nerve / surrounding tissue with be evaluated according to the following formula:

$$Relative Visibility of the Nerve \left( \% \right)= Grey Scale Value Ulnar Nerve/\frac{Grey Scale Values 0,3,6,9 o´clock}{4}$$

In addition to the graphical, software supported analysis, the Vienna Scoring System ^[[1]](#footnote-1),^^[[2]](#footnote-2)^ for descriptive evaluation of peripheral nerves will be used to mark differences of echotexture:

1. Internal Structure of the nerve visualized
2. The nerve is visualized as a circular or oval-shaped blight halo (epineurium)
3. The nerve is visualized as reflection determined by the anatomy of the surrounded tissue
4. The anatomical position of the nerve shows no response to the ultrasound beam (isoechoic behaviour)

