# Synopsis

| TITLE | **The Impact of Biological Gender in Peripheral Nerve Blockade: A Prospective Study in Volunteers** |
| --- | --- |
| Phase | IV |
| INVESTIGATIONAL PRODUCTS | **Drug:** Ropivacaine  ***Concentration:*** 7.5 mg/mL (0.75%) |
| BACKGROUND | To evaluate PD, PK and nerve-related morphometric differences of biological gender (male versus female) on nerve block characteristics |
| OBJECTIVES | **Primary Objective**   - Duration of sensory nerve blockade   **Secondary Objective**   - Pharmacokinetic characteristics (C_max_, t_max_, t_1/2_, AUC_0-6_, AUC0-∞) - Duration of motor blockade - Onset time of sensory nerve blockade - Onset time of motor blockade - Diameter of the ulnar nerve (absolute and relative to the BMI) - Visibility of the ulnar nerve in ultrasound (Grey-tone analysis ulnar nerve relative to the surrounding tissue) |
| DESIGN | Prospective, single-centre, interim-analysis after 2 x 12 cases |
| HYPOTHESIS | Null-hypothesis: biological gender (male or women) does not influence the primary outcome variable  Alterative-hypothesis: biological gender (male or women) influences the primary outcome variable |
| CONTRIBUTION TO THE CLINICAL PRACTICE | In the case of rejection of the null-hypothesis, peripheral regional anaesthesia techniques can be adapted to the particular biological gender and PD characteristics can be adapted to the respective clinical indication. |
| BLINDING-PROTOCOL | - |
| CENTER(S) / COUNTRY(IES) | 1 centre in Austria (Department of Clinical Pharmacology, Medical University of Vienna) |
| PATIENTS / GROUPS | 45 healthy male and 45 healthy female volunteers (total number of volunteers: 90). An interim-analysis will be after 12 male and 12 female volunteers. |
| INCLUSION CRITERIA | - Healthy males and females - Healthy, according to the medical history, ECG, vital signs, laboratory results and physical examination as determined by the Investigator/Sub-Investigator - Signed written informed consent prior to inclusion in the study - 18-55 years old inclusive - BMI: 18 to 35 kg/m^2^ - Ability to understand the full nature and purpose of the study, including possible risks and side effects - Ability to co-operate with the investigator and to comply with the requirements of the entire study - Availability to volunteer for the entire study duration and willing to adhere to all protocol requirements |

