### Secondary Outcome Parameters

To evaluate the differences in PK, PD (sensory and motor onset times, duration of motor blockade) and morphometric ulnar nerve characteristics between male and female study subjects.

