## Statistical Analysis

Pharmacodynamic data analysis: The primary outcome is duration of sensory block. Secondary outcomes include onset of sensory block, onset and duration of motor block.
Data will be presented as mean (SD), median [interquartiles] and count (%) and analysed using unpaired two-sided Student *t-*, Mann-Whitney *U-*, log-rank and Fisher exact statistics. Mixed effects linear models will be used to adjust for subject characteristics.

Pharmacokinetic data analysis: Secondary outcomes, including parameters such as C_max_, t_max_and AUC will be estimated and analysed using statistics as listed above.

Morphometric data analysis: Differences between grey scales of nerves and nerve visibility (differences between nerves and surrounding tissue) and differences in the Vienna Scoring System will be compared using unpaired two-sided Student *t-* or Mann-Whitney *U-* statistics as appropriate. Mixed effects linear models will be performed to determine the correlation of nerve visibility with morphometric variables.

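### Grey-scale nerve visibility, a secondary outcome compared between the sexes, is read off-line from stored images with no provision for masking the reader

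*Protocol*

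**What the plan says.** The Synopsis has a row labelled "BLINDING-PROTOCOL" that contains only a dash, and so does the Blinding section under Methods. No other section provides for a masked assessor, coded images or an independent reader.

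The section Nerve Measurements and Evaluation of Nerve Visibility sets out this sequence:

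- Live scan: "The nerve will be traced until optimal visibility is obtained", with brightness standardised by the machine's automatic gain.
- Size: "Thereafter the nerve circumference will be measured with the internal area measurement tool".
- Storage: "Figures will be stored as JPEG files with the ulnar nerve in the centre of the screen". The files are then analysed in Photoshop.
- Surrounding tissue: "the selected area will be moved to muscle and connective tissue around the nerve to the following positions", namely 3, 6, 9 and 12 o'clock. Relative visibility is the nerve's grey value divided by the mean of these four.
- In addition, the Vienna Scoring System, a four-category scale, is used "for descriptive evaluation of peripheral nerves will be used to mark differences of echotexture".

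Secondary Outcome Parameters includes differences in "morphometric ulnar nerve characteristics between male and female study subjects". Under Statistical Analysis, grey-scale visibility is compared between the groups, and "differences in the Vienna Scoring System will be compared using unpaired two-sided Student" t or Mann-Whitney tests. The section PD, PK and morphometric data analysis repeats this.

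**The concern.** Sex is the exposure in this study. It cannot be hidden from the person who scans, performs the block or tests the hand, so a general dash for blinding is understandable. The grey-scale reading is different: it is made later, on a computer, from a file. For that step the absence of masking is a choice and is not forced by the design.

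The reading also leaves room for judgement. The four clock positions are fixed, but the distance from the nerve is not, and nothing says which tissue to sample where muscle and connective tissue are both within reach. Those four areas form the denominator of the outcome. If the reader knows the sex and expects nerves to look different in men and women, the placement can drift in line with the contrast under test. Such a drift is systematic. Recruiting more volunteers does not average it out; it makes a spurious difference more likely to reach significance.

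**Working it through.** **Inputs from the protocol.** 45 men and 45 women (Synopsis); two-sided tests (Statistical Analysis); 5% level (Sample size calculation); visibility = nerve grey value / mean of four surround values (Nerve Measurements and Evaluation of Nerve Visibility).

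**Assumed.** A reading shift of b SD tied to sex, with no true sex difference. The protocol gives no SD for visibility and no reader error, so b is shown over a range.

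**1. The group size.** The plan sizes the trial on the primary outcome (difference 35 min, SD 54 min). The normal approximation gives n = 2 × (1.96 + 0.84)² × 54² / 35² ≈ 37.3, so 38 per group. The t-test version gives 39 (power 0.807; 0.796 with 38). Then 76 × 1.15 = 87.4 and 78 × 1.15 = 89.7, both consistent with 90 in total. The figure reproduces and is not in dispute. It matters here only because visibility is tested in the same 45 per group.

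**2. How far placement can move the ratio.** If k of the four areas fall on tissue darker by a fraction x, the ratio is multiplied by 1 / (1 − kx/4).

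- One area 20% darker: 1 / (1 − 0.05) = 1.053, a rise of 5.3%.
- All four 10% darker: 1 / (1 − 0.10) = 1.111, a rise of 11.1%.

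These are illustrations. Without an SD for the ratio they cannot be converted into SD units.

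**3. Effect on the false-positive rate.** Noncentrality = b × √(45/2) = 4.743 × b. The rejection rate is P(|Z + noncentrality| > 1.96).

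- b = 0.1: noncentrality 0.474; normal approximation 7.6%; noncentral t 7.6%.
- b = 0.2: noncentrality 0.949; normal approximation 15.8%; noncentral t 15.5%.
- b = 0: 5.0%.

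With only 12 per group, the size at the interim analysis, the noncentral t rates are 5.6% at b = 0.1 and 7.6% at b = 0.2. The same shift therefore does more harm in the larger sample. The interim analysis may change the final number, and these rates would move with it.

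**4. Which steps coding can reach.**

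- Grey-scale reading: from stored files, so it can be masked.
- Vienna score: the protocol does not say whether it is given live or from the stored image. It can be masked only if it is assigned from the image.
- Choice of frame: made live by someone who sees the volunteer, so it cannot be masked this way.
- Nerve size: listed before image storage and made with an internal measurement tool, so apparently on the machine and not masked.
- Pinprick and motor testing: necessarily open.

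**The case against.** The best case for the plan has four parts.

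First, the dash may simply mean not applicable. Randomization carries the same dash, and both groups receive the same injection. That is a fair reading, and nothing in the protocol contradicts itself on this point. But the dash still leaves the one readily maskable reading step without masking.

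Second, there are safeguards: four fixed clock positions, one selection moved to each, automatic gain, a common display scale, and in the Synopsis a median grey value over areas of similar nerve size. These limit the reader's freedom. They leave distance and tissue choice open.

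Third, the protocol does not say that the reader knows the sex. It names no reader and no file labels for images, and subject numbers run consecutively without encoding sex. This stands. Knowledge is likely if the scanner also reads, but it is an inference. It is likewise not stated that the nerve is outlined by hand; only the moving of the area is described.

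Fourth, the shift sizes are hypothetical, and at 0.1 SD the rate rises only from 5% to 7.6%. That also stands: the text shows that bias is possible, not that it occurs.

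A reader might go further and infer that the trial's main conclusion is at risk. The documents do not support that. The null and alternative hypotheses concern the primary outcome only, which is sensory block duration and does not depend on the image reading.

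**Conclusion.** The point holds for the off-line grey-scale visibility reading, and for the Vienna score only if that is assigned from stored images. No masking is planned for a reading that could be masked, that leaves placement partly to the operator, and that is tested between the sexes. If the reader knows the sex and shifts the readings by 0.1 to 0.2 SD, the false-positive rate of that secondary comparison would be about 7.6% to 16% instead of 5%, with 45 per group. Both the knowledge and the shift are assumptions.

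The sample size and the primary outcome are untouched. Nor would coding the files make all the morphometric data blinded, because frame selection and apparently nerve size are settled live. This is a worthwhile improvement to a secondary outcome and does not threaten the study's main result.

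**What to change.** In the Synopsis row, in the Blinding section under Methods, and in Nerve Measurements and Evaluation of Nerve Visibility, state that:

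- JPEGs are exported under a random code without subject number or sex, and mixed across the two groups;
- grey-scale visibility is read from the coded files without knowledge of sex and before linkage to block data;
- the Vienna score is assigned from the same coded images;
- image acquisition, on-machine nerve-size measurement, Pinprick testing and motor testing remain open.

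The same reader can be kept, but someone who also scanned may recognise images, so masking is then incomplete. Where an existing team member who did not scan is available, that person should read. The cost is the work of renaming and shuffling the files. Sample size, visits and volunteer burden do not change.

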## Pharmacokinetic Analysis

Blood samples: A 4-ml sample of blood (in Lithium-Heparin syringes) will be drawn from an antecubital vein for the determination of plasma ropivacaine concentrations at baseline and 20, 40, 60, 120, 240 and 360 min after performance of nerve blockade (7 blood samples). Blood samples will be kept on ice for a maximum of 60 min before being centrifuged at 4°C and 2600 g for 10 min to obtain plasma. Plasma sampling time points were chosen to capture C_max_ (previously described at t_max_ of 0.44 hours after local block) and terminal half-life (previously described as 2.12h).

The collected samples will be stored at minus 20°C for subsequent analysis. Ropivacaine concentrations in venous plasma will be determined by gas-chromatography/mass spectrometry (GC-MS). Briefly, 100 µL of plasma will be mixed with 100 µL internal standard solution (1,25 µg bupivacaine/mL phosphate buffer pH 7.4) and extracted with 700 µL of n-butyl chloride. The sample will be vortexed gently for 1 min, centrifuged and the supernatant will be transferred into a GC-MS vial.

The GC-MS system consists of a 7890B gas chromatograph coupled with a 7000C GS-MS/MS Triple Quad mass selective detector spectrometer (Agilent, Santa Clara, CA, USA). An autosampler G4513A will be used for splitless injection onto an Agilent J&W HP GC Column (30 m, 0.25 mm, 0.25 µm). The injection volume will be 2µL. Evaluation will be performed with Mass Hunter MS Quantitative Analysis software (Agilent, Santa Clara, CA, USA).

Pharmacokinetic data will be calculated and fitted using a commercially available computer program (Certara Phoenix PK Software). The following PK parameters will be determined: maximum concentration (Cmax), time to maximum concentration (tmax), terminal elimination half- life (t1⁄2), area under the concentration–time curve (AUC) for the sampling period of 6 h (AUC0-6), and the total AUC (AUC0-∞). The AUC for plasma and interstitium will be calculated from non-fitted data by employing the trapezoidal rule. When concentrations are below the lower detection limit for some of the time points, the AUC0-6 will be based on the area under the measurable concentrations. For plasma, apparent total body clearance (CL) and apparent volume of distribution (Vd) are also calculated.

## Objectives of the study

### Primary Outcome Parameter

To evaluate the difference between male and female study subjects in sensory block duration of the ulnar nerve.

### Secondary Outcome Parameters

To evaluate the differences in PK, PD (sensory and motor onset times, duration of motor blockade) and morphometric ulnar nerve characteristics between male and female study subjects.

